**1.10 Concomitant Therapy.**

All concomitant therapy are permitted, however caution is advised when zoledronic acid is given together with aminoglycosides, non-steroid anti-inflammatory drugs (NSAID), or other potential nephrotoxic drugs, as both MM in itself and zoledronic acid are potentially nephrotoxic.

**1.11** **Study Drug Information.**

The study drug, zoledronic acid, is commercially available and approved by EMEA. The study drug is given as intravenous infusion at the local hematologic department and handled according to local routine. No study drugs are handed over to the patients. For details, see appendix 5

**1.12 Withdrawal from the Study.**

In accordance with the current revision of the Declaration of Helsinki and applicable regulations, a

patient has the right to withdraw from the study at any time for any reason without prejudice to

his/her future medical care by the physician or at the institution.

Patients may be excluded from study in case of:

-significant protocol violation or non-compliance

-refusal of the patient to continue treatment and observations; withdrawal of consent

-if the investigator believes that for safety reasons (e.g., adverse events), it is in the best interest of the subject to stop treatment.

-if the patient due to renal failure is unable to receive zoledronic acid in two consecutive months (infusion can be delayed for up to three months). In case of tooth extraction, a delay of up to four months is allowed.

-if the patient due to BON stops treatment with zoledronic acid.

-if patients in the control arm experience progressive bone disease and the treating physician find it in the best interest of the patient to reinitiate treatment with zoledronic acid.

-if the subject becomes pregnant

-death

Patients excluded from the study will be followed for 30 days by the local hospital to insure registration of late occurring AE, SAE, SAR and SUSARs

The date and the reason for withdrawal status should be stated in the case report form. If the patient withdraws his or / her consent no further investigations will be conducted. If the patient is excluded for other reasons and it poses no risk for the patient fasting serum bone marker should be measured upon withdrawal, and bone imaging should be conducted no less than one month after withdrawal from the study. Data collected from the patient up until the time of withdrawal will if possible be used in the final evaluation of the study result unless the patient states it otherwise.

As stated in section 1.13, 286 patients need to be randomised to achieve enough power in the study. Patients will be included until this number is reached

**1.13 Statistical Considerations.**

Primary endpoint:

There are no published data on the incidence on PBD from year 2 and onward in MM. However, there are data showing the annual incidence of the more strict sPBD is approximately 5% in patients receiving continuous zoledronic acid [[31](#_ENREF_31)]. Since we in this study use a less strict definition of progression in bone disease, we assume the annual incidence will be 7.5% instead of only 5% in patients receiving zoledronic acid. Based on data from the MRC IX trial and from an ASH publication in 2012 we expect to see risk reduction rate of 0.5 [[32](#_ENREF_32)]. With a significance threshold of 0.05, one-sided, a power of 80, and a fixed study duration of 2 years, we need a sample size of 143 per group to detect a difference in the primary endpoint. 286 patients in total need to be allocated to the two treatment arms. However, due to the nature of the disease, 30% of all patients will be dead before year two. Due to the in- and exclusion criteria we presume that only 20% of the study population will be dead before stratification. Thus 358 patients in total need to be included in the protocol. Data will be analysed according to the treatment the patients actually received using the Kaplan-Meier analysis. Patients will be analysed per protocol. New data have shown significant reduction in PBD after 4 years treatment with zoledronic acid compared to 2 years of treatment in 170 randomised patients^33^.

Other endpoints:

Serum samples will be collected and stored from all patients. From the calculations above, we expect 32 cases of PBD during year two to four. Bone markers will be measured on these patients from the time of PBD and 6 month prior to the bone event. An equal number of controls will be selected as the number of cases PBD actually observed and bone markers will be measured likewise in these patients. The controls will be selected according the stratification criteria’s (previous autologous stem cell treatment, presence or absence of bone disease at diagnosis, and previous treatment with bortezomib). If multiple options are present the same gender will be chosen, and after that the closest age related. Data will be analyzed as a case control study

Sites may participate in the study even if they only evaluate bone disease using either conventional radiography or low-dose CT. Since this part of the study is mainly descriptive, no statistical cut-off values have been defined. We expect however, that at least half of the patients will be evaluated using both modalities. All patients will have bone imaging conducted at the time points specified in appendix 1. Each patient will function as his or her own control since we will look for discrepancies between the different modalities, and the development in these discrepancies over time. Data will be analysed using the student t-test.

Amendment: The amendment will have no impact on the statistical consideration since all patients will be randomised. Only the part of the study comparing low-dose CT to conventional radiography will be affected. This part of the study however is descriptive and each patient function as his or her own control no statistical changes need to be made.

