If no local instruction exists, please see the Summary of Product Characteristics at EMEA. In brief it states: *zoledronic acid 4 mg should be given as a single intravenous infusion in no less than 15 minutes. To prevent hypocalcaemia patients should also be administered an oral calcium supplement of 500 mg and 400 IU vitamin D daily. When initiating treatment with zoledronic, serum creatinine and creatinine clearance (CLcr) should be determined. CLcr is calculated from serum creatinine using the Cockcroft-Gault formula. Zoledronic is not recommended for patients presenting with severe renal impairment prior to initiation of therapy, which is defined for this population as CLcr < 30 ml/min. In patients presenting with mild to moderate renal impairment defined as CLcr 30–60 ml/min, the following zoledronic acid dose is recommended:*

| **Baseline creatinine clearance (ml/min)** | **Zoledronic acid recommended dose*** |
| --- | --- |
| > 60 | 4.0 mg zoledronic acid |
| 50–60 | 3.5 mg* zoledronic acid |
| 40–49 | 3.3 mg* zoledronic acid |
| 30–39 | 3.0 mg* zoledronic acid |

- Doses have been calculated assuming target AUC of 0.66 (mg•hr/l) (CLcr = 75 ml/min). The reduced doses for patients with renal impairment are expected to achieve the same AUC as that seen in patients with creatinine clearance of 75 ml/min.

*Following initiation of therapy, serum creatinine should be measured prior to each dose of zoledronic acid and treatment should be withheld if renal function has deteriorated. In the clinical trials, renal deterioration was defined as follows:*

*- For patients with normal baseline serum creatinine (< 1.4 mg/dl or < 124 μmol/l), an increase of 0.5 mg/dl or 44 μmol/l;*

*- For patients with abnormal baseline creatinine (> 1.4 mg/dl or > 124 μmol/l), an increase of 1.0 mg/dl or 88 μmol/l.*

*In the clinical studies, zoledronic acid treatment was resumed only when the creatinine level returned to within 10% of the baseline value. Zoledronic acid treatment should be resumed at the same dose as that given prior to treatment interruption.*

For further details see appendix 5.

If infusion of bisphosphonate for any reason is delayed for more that two months (meaning more that three months between two infusions) e.g. due to deteriorating renal function the patient will be excluded from the study.

Amendment:

Patients included according to the amendment will have a smaller radiation exposure 32.5-39 mSv instead of 45.5-52 mSv

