**1.9 Side Effects.**

Zoledronic acid has been approved by EMEA since 2001 for prevention of SRE in adult patients with advanced malignancies involving the bone. It has been used extensively for many years and has a well-known toxicity profile. It is not financially possible to conduct a new study where all possible side effects will be reported rigorous, as no pharmaceutical companies have shown interest in the study. Furthermore, it is unlikely that new – still unknown – side effects can be identified from this study since all patients most likely will receive multiple lines of anti-myeloma chemotherapeutics that will differ from site to site, and a significant portion of the patients will die due to progressive disease during the protocol. However, the Nordic Myeloma Study Group finds it very relevant to conduct a study with focus on BON, which is a late occurring, severely disabling side effect where the incidence increases proportionally to the exposure time. In this study, we will focus on BON and renal insufficiency as this is a common clinically relevant side effect to zoledronic acid. Patients will furthermore be evaluated using QoL, which ultimately will answer the question whether prolonged treatment with zoledronic acid is of benefit for these severely ill patients. All AEs and SAEs will be documented in the patient’s medical journal but will not be reported in the CRF if they can be related to the myeloma disease or to the chemotherapeutic treatment the patient receives. All SAR and SUSAR will be reported in the CRF. The treating physician decides if an AE or SAE is related to the investigational compound and thus should be reported as an SAR / SUSAR. Summary of Product Characteristics supplied in appendix 5 will be used as reference document to decide if a SAR should be upgraded to a SUSAR. All cases of renal insufficiency, BON, hypo-, and hypercalcaemia, will be reported in the CRF regardless of causality.

Registration of predefined (section 1.9.1 and 1.9.2) AEs, SAEs, SAR, and SUSARs will continue until the last infusions at year 4 +30 days for the treatment group or until year 4 +30 days for the observation group.

All national SAE, SAR, and SUSARs reported in the CRF during the trial will be listed and reported yearly by the national investigator to the National Health Authority and to the National Ethics Committee according to the national regulations by the national study secretary.

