**1.14 Ethical Considerations**

Multiple myeloma remains an incurable malignant disorder; however the average expected lifetime is increasing due to improved treatment. Treatment monthly with zoledronic acid is known to reduce the risk pathological fractures, progressive osteolysis, and to reduce pain. No knowledge exists on what should be done after two years of treatment. Prolonged treatment carries the risk of BON, whereas discontinuation of treatment probably increases the risk of PBD. The primary purpose of the study is to investigate if prolonged treatment with zoledronic acid provides adequate protection against PBD to justify an increased risk of BON. To investigate this, patients will be randomized 1:1 to receive either 2 or 4 years of treatment. To protect participating patients from both under- overtreatment, routine oral cavity examinations and bone imaging are planned in the protocol. Bone imaging is balanced between early detection of PBD (and thus possible removal from the protocol) and minimal radiation exposure. It is estimated that a patients will receive an excess radiation dose of 33.2 – 36.6 mSv equal to the dose received from 1.5 conventional CT. This radiation exposure is not ignorable. The median age of a newly diagnosed patient however is approximately 70 years, they all suffer from an incurable cancer and have a severely reduced life expectancy. This reduces the long-term risk of secondary malignancies due to radiation exposure to approximately 0.0175%. Furthermore, the additional bone imaging will not only help us decide if the more sensitive modality low-dose CT in the future should replace conventional radiography, it will also help determining if serum samples partly can replace bone imaging, thus reducing future radiation exposure. Most importantly, it will in the actual patient help us detect progressive bone disease before this becomes symptomatic due to e.g. vertebral collapse or pathological fractures.

An additional part of the study is to investigate if serum bone markers can be used to tailor treatment with zoledronic acid in the individual patients in the future. To investigate this, extra serum will be collected and stored for later analysis. This extra serum will be collected when blood samples to monitor the myeloma disease are collected anyway, thus no additional appearances at the outpatient clinic for blood draws over the course of the study are anticipated.

REGULATORY ETHICS COMPLIANCE

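### The sample size in 1.13 leaves no room for deaths and exclusions after randomisation, so 286 randomised patients give somewhat less than the stated 80% power

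*Protocol*

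**What the plan says.** Protocol section 1.13 sets the primary-endpoint sample size from these inputs:

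- PBD incidence under continued treatment: "we assume the annual incidence will be 7.5% instead of only 5% in patients receiving zoledronic acid".
- Effect: "we expect to see risk reduction rate of 0.5".
- Test and follow-up: "With a significance threshold of 0.05, one-sided, a power of 80, and a fixed study duration of 2 years".
- Result: "a power of 80, and a fixed study duration of 2 years, we need a sample size of 143 per group", so 286 randomised.

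Section 1.13 then presumes that 20% die before randomisation and raises the number included to 358. Section 1.12 repeats that 286 is the number to randomise for adequate power. No loss between year 2 and year 4 is mentioned.

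Other sections foresee such loss:

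- Section 1.9 on deaths: "a significant portion of the patients will die due to progressive disease during the protocol".
- Section 1.6 (amendment) admits patients directly to randomisation with a remaining life expectancy of one year or more, although follow-up lasts two years.
- Section 1.8 on infusion gaps: "e.g. due to deteriorating renal function the patient will be excluded from the study". Section 1.7 has the same rule for years 2 to 4.
- Section 1.12 adds exclusion for BON with treatment stopped, safety, non-compliance and withdrawal of consent.

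Section 1.5 does not count death as PBD. Section 1.13 specifies a per-protocol analysis.

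**The concern.** A patient who dies without PBD, or leaves the study, adds no further PBD risk time. If the 143 assumes two complete years for everyone, each such loss removes expected events and lowers power below the advertised value, even when all 286 patients are randomised and the incidence and effect assumptions are right. A null result would then be read against a sensitivity that the trial did not have. The direction follows from the protocol's own text. The size does not, because no rate is given for years 2 to 4.

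**Working it through.** **Inputs.** From 1.13: hazard 0.075 per year with continued treatment; 0.15 per year after stopping (0.075/0.5); one-sided 5% (z = 1.645); 80% power (z = 0.842); two years of follow-up. From 1.14, the allocation: "patients will be randomized 1:1 to receive either 2 or 4 years of treatment". Assumption, not in the protocol: 10 to 30% lost over years 2 to 4. The values 20% and 30% are the protocol's own mortality figures for years 0 to 2, carried forward.

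**Step 1: reproduce 143.** With full follow-up the two-year PBD probabilities are

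- stop arm: 1 − exp(−0.30) = 0.2592
- continue arm: 1 − exp(−0.15) = 0.1393

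The log-hazard-ratio formula gives

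n = (1.645 + 0.842)² × (1/0.2592 + 1/0.1393) / (ln 2)² = 6.183 × 11.037 / 0.4805 = 142.03, rounded up to 143.

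Expected events: 143 × (0.2592 + 0.1393) = 57.0. Power with 143 per group: 80.2%.

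**Step 2: trace the allowance.** 286/0.80 = 357.5, rounded up to 358. The whole 20% is spent before randomisation.

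**Step 3: add loss after randomisation.** Take a loss hazard m = −ln(1 − loss)/2, equal in both arms and independent of PBD. The probability of an observed PBD with hazard l becomes

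p = l/(l + m) × (1 − exp(−2(l + m))).

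At 20% loss, m = 0.1116, which gives p = 0.2336 and 0.1252. Events are 143 × 0.3588 = 51.3, and the Step 1 formula then asks for 157.9 per group.

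Power with 143 per group, in percent:

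| Loss, years 2–4 | PBD events | Formula giving 143 | Freedman | Schoenfeld | Log-rank simulation |
|---|---|---|---|---|---|
| 0% | 57.0 | 80.2 | 80.8 | 83.4 | about 82 |
| 10% | 54.2 | 78.5 | 79.1 | 81.8 | about 80 |
| 20% | 51.3 | 76.5 | 77.1 | 79.9 | about 78 |
| 30% | 48.3 | 74.2 | 74.9 | 77.7 | about 76 |

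Separate simulation runs differ by about one percentage point.

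**Step 4: where power crosses 80%.** By the formula that gives 143, between 1% and 2% loss (it asks for 142.7 and 143.4 per group). By Freedman, about 5%. By Schoenfeld, about 19.5%.

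**Step 5: event count.** Section 1.13 states 32 expected PBD cases as following from its calculation, and 1.15 repeats 32 cases and 32 controls. The inputs imply about 57 over two years. The 32 equals 286 × 11.25% = 32.2, where 11.25% is the mean of 7.5% and 15%, that is, about one year's incidence rather than two.

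**The case against.** The protocol names no formula, and the choice matters. Schoenfeld with about 19.5% loss also lands on 143 and keeps power at 79.9% when 20% are lost; Freedman lands there with 5% loss. So 143 is numerically compatible with a calculation that already contained attrition. That point stands as arithmetic, and the absence of an allowance is an inference. It does not rescue the text, because 1.13 names no such loss and its one stated allowance is fully used before randomisation.

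If 7.5% and 15% are read as annual risks that compound, 143 per group gives 86 to 89% power with full follow-up and stays above 80% up to about 33% loss by Freedman. But that reading needs only 109 to 119 per group by the time-to-event formulas, so it does not explain the 143.

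The loss rates are assumed. The sentence in 1.9 covers all four years, including deaths already allowed for, and patients randomised at year 2 are selected survivors without recent PBD. Deaths from progressive disease may also follow a PBD already detected, because 1.7 requires imaging at relapse and 1.12 asks for imaging around withdrawal and keeps the data collected until then. Independent loss may therefore overstate the events forgone. Control patients excluded because PBD led to renewed treatment have already had the event and cost no power. All of this limits the size of the shortfall but does not remove it.

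**Conclusion.** The point holds, at moderate size. The 80% in 1.13 has no stated margin for losses that the same protocol foresees after randomisation. At an assumed 20 to 30% loss, power is about 74 to 80% depending on the formula; at 10% it is about 78 to 82%. This rests on constant hazards of 0.15 and 0.075, loss that is equal across arms and independent of PBD, and a loss rate that the protocol does not supply.

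A reader might infer three stronger things that the document does not support:

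- That 143 is miscalculated. It is not; it follows from the stated inputs.
- That power falls to the low seventies because continuing patients are excluded more often. No exclusion rate for that arm is given.
- That the 32 cases show far lower power. The protocol uses that number to size the bone-marker case-control comparison, not the primary test. It is an inconsistency to reconcile, not a design value for power.

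**What to change.** Keep 286 randomised. In section 1.13:

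1. State the sample-size formula and the assumed share of randomised patients lost to death or exclusion between year 2 and year 4.
2. Restate the power at that loss. At 20 to 30% it would be about 74 to 80%, depending on the formula.
3. Give the expected PBD count that follows (about 51 at 20% loss, 48 at 30%) and reconcile it with the 32 cases in 1.13 and the 32 cases and 32 controls in 1.15, so that the protocol does not carry two conflicting event counts.

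The cost is a few sentences and a slightly less favourable stated power. No extra patients and no change to treatment or follow-up are needed.

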Any radiological signs of bone disease including osteolysis (at least 10 mm), osteopenia, halisteresis, fractures including vertebral compression fractures (these findings are not necessarily equal to a Myeloma Defining Bone Disease Event; which is defined according to the International Myeloma Working Group Consensus Statement Paris 2011). No bone disease / Bone disease can be diagnosed on either conventional radiography or low-dose CT

QoL:

Quality of Life is evaluated using the European Organization for Research and Treatment of Cancer Quality of Life Questionnaire-Core 30 (EORTC QLQ-C30, version 3.0, together with the MY20 multiple myeloma specific supplement.

Primary Endpoint:

To compare the time to PBD from year 2 to year 4 in patients treated with monthly zoledronic acid in two consecutive years compared to patients treated with monthly zoledronic acid in four consecutive years.

Secondary Endpoints:

To compare the incidence of PBD from year 2 to year 4 in patients treated with monthly zoledronic acid in two consecutive years compared to patients treated with monthly zoledronic acid in four consecutive years.

To compare the incidence of sPBD from year 2 to year 4 in patients treated with monthly zoledronic acid in two consecutive years compared to patients treated with monthly zoledronic acid in four consecutive years.

To compare the incidence of bone healing from year 2 to year 4 in patients treated with monthly zoledronic acid in two consecutive years compared to patients treated with monthly zoledronic acid in four consecutive years.

To compare the overall survival from year 2 to year 4 in patients treated with monthly zoledronic acid in two consecutive years compared to patients treated with monthly zoledronic acid in four consecutive years.

To compare the incidence of BON from year 2 to year 4 in patients treated with monthly zoledronic acid in two consecutive years compared to patients treated with monthly zoledronic acid in four consecutive years.

To compare the development in QoL from year 2 to year 4 in patients treated with monthly zoledronic acid in two consecutive years compared to patients treated with monthly zoledronic acid in four consecutive years.

To compare the development in the bone markers CTX-I, PINP, bALP, and TRAP5b from year 2 to year 4 in the patients groups randomised to receive two or four years of treatment with zoledronic acid

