Fasting serum bone markers will be collected bi–annually. All time-points can be moved +/- 2 weeks.

Measurements of creatinine and calcium may be conducted up till 2 weeks before the visit

QoL questionnaire QLQ-C30 and MY20 will be used bi-annularly. All time-points can be moved +/- 2 weeks.

Infusion with zoledronic acid should be given ever 4^th^ week (+/- 1 week). Infusion can be delayed for up to 2 months e.g. due to temporarily impaired renal function (meaning a three month pause between two infusion is allowed). If infusions cannot be given within this time period the patient will be excluded from the study. If infusions are delayed for a significant period, it is the time passed and not the number of infusions that is relevant as to when stratification occurs.

Randomisation:

At year 2 patients will be randomised to A) stop treatment with zoledronic acid or to B) continue treatment with monthly infusions of zoledronic acid for another 2 years period (4 years in total). Randomisation is allowed to be moved -1months/+2months. The randomisation procedure will be stratified according to previous autologous stem cell treatment, presence or absence of bone disease at diagnosis, and previous treatment with bortezomib. Randomisation will take place at The Hematological Research Unit, Odense University Hospital, Denmark. For further details see appendix 6 (SOP for randomisation).

Planned visits, year 2-4:

Bone imaging will be conducted after 2½ years, after 3 years, after 3½ years, and after 4 years. All time-points can be moved +/- 1 month. In case of myeloma relapse requiring active treatment, new bone imaging should be conducted within a one-month time frame of initiation of new anti-myeloma treatment. If bone imaging has been conducted as part of relapse evaluation no less than three month prior to routine bone imaging time point,no new bone imaging need to be conducted. If any bone imaging, conducted from year 2 to 4, reveals PBD in patients not receiving zoledronic acid and the treating physician find it necessary to reinitiate treatment with zoledronic acid, the patient will be excluded from the study. In that case, fasting serum bone markers should be measured prior to re-initiation of zoledronic acid treatment. If bone imaging, conducted as part of a myeloma relapse evaluation in patients not receiving zoledronic acid, results in “no PBD”, treatment with zoledronic acid should *not* be re-initiated.

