Bone imaging should be conducted using both conventional radiography and low-dose CT. Sites however may participate in the study without conducting both conventional radiography and low-dose CT. In this case, the chosen modality must be used consistently throughout the entire study period.

Fasting serum bone markers should be collected every fourth week (+/- 1 week) throughout this period. Serum samples do not need to be collected at the exact date of zoledronic acid infusion but can be collected up to two weeks prior to infusion; serum samples however must not be collected after zoledronic acid infusion. Measurements of creatinine and calcium may be conducted up till 2 weeks before the visit

QoL questionnaire QLQ-C30 and MY20 will be used every 3^rd^ month: after 27, 30, 33, 36, 39, 42, 45, and after 48 months. All time-points can be moved -2 weeks.

Infusion with zoledronic acid in the treatment arm should be given ever 4^th^ week (+/- 1 week). Infusion can be delayed for up to 2 months e.g. due to temporarily impaired renal function (meaning a three month pause between two infusion is allowed). If infusions cannot be given within this time period the patient will be excluded from the study.

For specific instructions concerning conventional radiography and low-dose CT, see appendix 2

For specific instructions concerning serum bone makers, see appendix 3

Amendment:

Patients who are included after 23-25 zoledronic acid infusions outside protocol will move directly to randomisation. The randomisation procedure will be stratified according to previous autologous stem cell treatment, presence or absence of bone disease at diagnosis, and previous treatment with bortezomib. Randomisation will take place at The Hematological Research Unit, Odense University Hospital, Denmark. For further details see appendix 6 (SOP for randomisation).

Acquiring source data (amendment):

Bone imaging must not be done more than two months prior to inclusion and should be done no more than one month after inclusion.

Fasting serum bone markers must be collected no more that 2 weeks after inclusion.

QoL questionnaire QLQ-C30 and MY20 should be completed no more that 2 weeks after inclusion.

Investigation according to local guideline for any pre-existing BON must be conducted before inclusion in the protocol amendment

Planned visits, year 2-4: (amendment)

No changes compared to original description.

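### The only primary analysis is both as-treated and per-protocol, while treatment-related exits before PBD can occur only in the zoledronic acid arm and follow-up then ends

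*Protocol*

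**What the plan says.** - **Objective.** Section 1.5 gives the primary endpoint: "To compare the time to PBD from year 2 to year 4 in patients treated with monthly zoledronic acid in two consecutive years", against four consecutive years. Patients are randomised 1:1 at year 2 to stop (arm A) or continue (arm B).
- **Analysis.** Section 1.13: "Data will be analysed according to the treatment the patients actually received using the Kaplan-Meier analysis. Patients will be analysed per protocol". The protocol names no intention-to-treat or by-randomised-arm analysis.
- **Design figures.** Section 1.13: "With a significance threshold of 0.05, one-sided, a power of 80, and a fixed study duration of 2 years", giving 143 per group and 286 randomised.
- **Exits tied to treatment.** Section 1.7 says of infusion delays in years 2-4: "If infusions cannot be given within this time period the patient will be excluded from the study". Section 1.8 repeats a delay rule. Section 1.12 adds renal failure, a safety stop, and the case "if the patient due to BON stops treatment with zoledronic acid".
- **Exit specific to arm A.** Sections 1.7 and 1.12: an observation-arm patient leaves if PBD is found and the physician restarts zoledronic acid.
- **After exit.** Section 1.12 keeps data up to withdrawal where possible. It adds 30 days of safety follow-up and, if consent is not withdrawn and there is no risk to the patient, one bone imaging and one marker sample. Section 1.6 plans no further protocol follow-up.

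**The concern.** The trial asks whether a policy of four years prevents PBD better than a policy of two. Randomisation makes the arms comparable at year 2 only if patients are then counted where they were assigned and observed until the endpoint or year 4. The protocol secures neither.

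The two sentences in section 1.13 also disagree. Take an arm B patient who stops early. An as-treated analysis could move that patient to the other group or split the follow-up time; a per-protocol analysis would remove or censor the patient. Nothing says which governs, so the choice could be made after the data are seen in an open-label trial.

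If the patients who leave arm B have a different PBD risk from those who stay, the hazard ratio no longer estimates the effect of the policy, and the one-sided 5% error rate is no longer guaranteed. Because follow-up ends at exit, the missing PBD data could not be recovered later.

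**Working it through.** **1. Reproduce the sample size.** Inputs from section 1.13: annual PBD incidence 7.5% on zoledronic acid; risk ratio 0.5, hence 15% in the observation arm; 2 years; one-sided 0.05; power 80%. Treat the incidences as exponential hazards:
- P(A) = 1 - exp(-0.15 × 2) = 0.2592
- P(B) = 1 - exp(-0.075 × 2) = 0.1393
- n per arm = (1.645 + 0.842)² × (1/0.2592 + 1/0.1393) / (ln 0.5)² = 142.03, rounded up to 143

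This matches, and 286/0.80 = 357.5, rounded up to 358, also matches. The 20% allowance covers loss before randomisation; nothing is allowed for loss after it.

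**2. Who can leave before the primary event?**

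| Rule | Section | Arm affected after randomisation | Before PBD? |
|---|---|---|---|
| Infusion delay too long | 1.7, 1.8 | B only | Yes |
| Renal failure, infusions missed | 1.12 | B only | Yes |
| BON with treatment stop | 1.8, 1.12 | B only | Yes |
| Safety stop of treatment | 1.12 | B only | Yes |
| Restart of zoledronic acid after PBD | 1.7, 1.12 | A only | No, the event has occurred |
| Violation, consent withdrawal, pregnancy, death | 1.12 | Both | Yes |

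The treatment-related exits before PBD are one-sided by construction.

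**3. What could this do?** The protocol gives no exit rate after randomisation and no link between exit and PBD risk, so everything in this step rests on assumptions. Assume no true effect, 143 per arm, 15% PBD per year, 2 years, and a lognormal frailty (log-SD 1) that drives both PBD and arm B exit. A one-sided 5% log-rank test then gives the following, as ranges over repeated simulations:

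| Arm B exits | Handling | Hazard ratio | False positives |
|---|---|---|---|
| None | - | 1.00 | about 5% |
| 3% per year | censored at exit | 0.96-0.99 (runs at 2-5% per year) | about 6% |
| 10% per year | censored at exit | 0.92-0.93 | about 8-9% |
| 20% per year | censored at exit | 0.86-0.88 | about 12-13% |
| 10-20% per year | deleted from the set | 1.00 | about 5% |
| 10-20% per year | followed to year 4, analysed as randomised | 1.00 | about 5% |

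A second model assumes that 30% of patients are frail with 2-3 times the PBD risk, and that exits occur only among frail arm B patients (10-20% of the arm). Censoring gives 6-10% false positives (hazard ratio 0.98-0.92). Deletion gives 8-22% (0.94-0.79). If exit is unrelated to PBD risk, the rate stays near 5%.

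The two models disagree about deletion but agree about censoring and about the cure.

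**4. Does relabelling the set suffice?** No. With no imaging after exit, an intention-to-treat analysis would censor the same patients at about the same dates. The error rate returns to about 5% only when PBD assessment continues.

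**5. Power under the remedy.** Suppose a fraction x of arm B stops at one year and then has the observation-arm hazard. Arm B's 2-year PBD-free probability is S = (1 - x)exp(-0.15) + x·exp(-0.225), and the average hazard ratio is (-ln S / 2)/0.15.

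| x | Average hazard ratio | Power at 143 per arm | n per arm for 80% |
|---|---|---|---|
| 10% | 0.52 | 76% | 160 |
| 20% | 0.55 | 72% | 180 |
| 30% | 0.57 | 67% | 204 |

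**The case against.** **Direction.** A reader might infer that the analysis must make four years look better, because the sickest arm B patients disappear. The documents do not support that as fact. Section 1.3 ties BON to treatment duration, drug potency and tooth extraction. Sections 1.8 and 1.9 treat renal impairment as a drug side effect; only section 1.10 adds that myeloma is itself potentially nephrotoxic. The opposite bias is also possible. If per-protocol means deleting observation-arm patients who restart after PBD, arm A events are lost. If an arm A patient restarts at a relapse without PBD, contrary to section 1.7, that patient could be reclassified or removed. This objection stands.

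**Size.** Exit rates of 10-20% per year have no anchor in the protocol. Randomisation already requires at least 12 infusions in two years and adequate renal function. Amendment patients need 23-25 infusions and no earlier BON. At 2-5% exits per year the false-positive rate is only 6-7%. This stands too.

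**Handling.** Section 1.12 keeps data up to withdrawal, which points to censoring rather than deletion. That is a fair reading, but the censoring can still be informative.

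**Stratification.** A reader might infer from the stratified randomisation in section 1.7, "The randomisation procedure will be stratified according to previous autologous stem cell treatment, presence or absence of bone disease at diagnosis", that section 1.13 fixes an unstratified test. It names only a Kaplan-Meier analysis. The choice of test and its stratification may properly be left to the analysis plan.

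None of this reaches the core. The protocol itself fixes the analysis set, so the set is not a detail left open for the analysis plan.

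**Conclusion.** The point holds, and the text should be changed before analysis. As written, the sole primary analysis of a randomised superiority comparison uses two incompatible non-randomised sets. The treatment-related exits before PBD are confined to one arm, and follow-up ends at exit. That leaves the comparison open to one-sided informative censoring.

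This loss of protection follows from the text alone. The amount of bias does not: the simulated excess, from about one to eight percentage points of false positives under the frailty model with censoring, depends entirely on the assumed frailty and exit rates. It vanishes if exits are unrelated to PBD risk. The calculation of 143 per group is not in dispute here.

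**What to change.** 1. Replace the two sentences in section 1.13 with wording such as: *The primary analysis of time to PBD includes all randomised patients in the arm to which they were assigned, regardless of the zoledronic acid they received. A per-protocol analysis, with its set defined in advance, is a sensitivity analysis.*
2. Amend sections 1.6, 1.7 and 1.12 so that stopping or restarting zoledronic acid ends study treatment but not study follow-up. Unless consent is withdrawn, the PBD imaging scheduled in section 1.7 continues to year 4. This also preserves follow-up for the secondary endpoints in arm A patients who restart.
3. Reconcile the delay limits, which decide who leaves. Section 1.7 allows a two-month delay (a three-month gap). The drug-administration part of section 1.8 applies that limit for any reason. The BON part of section 1.8 allows a four-month pause around tooth extraction. Section 1.12 cites two consecutive missed months together with a three-month delay, and four months for extraction.

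**Cost.** This is more than a change of wording. It alters the withdrawal rules and requires imaging of patients who have stopped, although only at visits already planned for those who complete. It also dilutes the effect: if 10-30% of arm B stop at one year and then have the observation-arm hazard, power at 143 per arm falls from 80% to about 76-67%. The sponsor should state an expected stopping rate and decide whether 286 randomised patients still suffice.
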